### ***13.1.7 Pharmacodynamic Analysis***

The changes in IENFD between the baseline and terminal samples for each subject will be calculated and within-group change will be tested using a 2-tailed paired t test, with any result

with a  $P < .05$  being considered significant. Analysis of changes from baseline to end of study results for the Norfolk-QOL-DN (and subset score analysis), Toronto Clinical Neuropathy Score, modified Toronto Clinical Neuropathy Score, quantitative thermal threshold, and quantitative vibrations perception will be outlined in the statistical analysis plan.

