### **4.2 Secondary Objectives**

The secondary objectives of the study are:

- To evaluate the efficacy of WST-057 to increase intraepidermal nerve fiber density (IENFD) present in punch biopsies collected from the dosing area/treated skin (calf) at weeks 0 and 24 within the same subject.
- To determine the impact (defined as change from baseline) of once-daily topical dosing of WST-057 on quality of life measures using the Norfolk-QOL-DN (Total Score), Norfolk-QOL-DN Physical/Large Fiber Function, Small Fiber Function, Activities of Daily Living, and Symptoms subsets scores at week 24.

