#### **Patient Check-in (Baseline/Day 1)**

If during the Baseline visit, a subject fails to meet any inclusion or exclusion criteria, then the Investigator is not required to complete the remaining visit activities. On the morning of day 1 (predose), the following procedures will be performed:

- Review of IENFD results from the screening calf biopsy (accepted if  $> 1$  and  $< 10$  IENF/mm)
- Verify baseline biopsy site has healed (prior to dosing phase)
- Medical history review
- Inclusion/exclusion review
- Urine drug screen and alcohol breathalyzer
- Urine dipstick pregnancy test
- Concomitant medications and AEs
- Physical examination and body weight, height, BMI calculation
- Supine and standing vital signs
- Toronto Clinical Neuropathy Score
- Modified Toronto Clinical Neuropathy Score
- 12-lead ECG
- Clinical laboratory tests (hematology, clinical chemistry, urinalysis)

- Serology for hepatitis B surface antigen, hepatitis C antibody, HIV 1 & 2 antibody
- Quantitative thermal threshold
- Quantitative vibration perception
- Visual Analogue Score
- Sural nerve testing
- Quality of Life (Norfolk-QOL-DN)
- Dermal Draize Score (baseline/day 1)
- Randomization and receipt of assigned bottle of investigative product
- Instruct subjects on the proper storage and self-administration of study drug
- Patient training on the topical application of investigational drug

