#### 7.1.1 *Intraepidermal Nerve Fiber Density*

Change in IENFD from baseline to week 24 within each subject will be evaluated via a skin punch biopsy. The baseline punch biopsy will be collected at least 28 days prior to study day 1, such that the biopsy healing can be monitored and confirmed prior to first dose administration.

The skin punch biopsies should be performed in the calf approximately 10 cm above the lateral malleolus and 3 cm to the posterior; and in the thigh approximately 25 cm below the iliac spine, 5 cm below the level of the pubis, and 8 cm to the posterior, using a 3 mm disposable punch under sterile technique after topical anesthesia with lidocaine. The biopsy should be shallow (3 to 4 mm), and should require no suture ([Lauria et al, 2010](#)).

If possible, the end-of-study biopsy should be collected no less than 2 cm and no more than 3.5 cm from the initial biopsy site from the same leg as the screening biopsies. Additional biopsy collection details will be outlined in a study procedure document provided to the site.

Upon collection, the biopsy should be immediately fixed in cold Zamboni's fixative solution and stored overnight in a 4°C refrigerator. The biopsy should remain in this chilled fixative for a minimum of 12 hours and a maximum of 24 hours. Next, the fixed skin sample should be transferred to chilled cryovial containing 1 × phosphate buffered saline (PBS) with 15% sucrose. Additional processing details will be outlined in a study procedure document provided to the site.

The sample will then be shipped with a wet ice pack in an insulated container for central processing to the following address:

WinSanTor, Inc  
Attn: [name] (UCSD)  
[name]

[name]  
United States of America  
[contact]

Upon receipt at the laboratory, the samples will be transferred to a labeled cryovial containing 1 × PBS with 30% sucrose and stored in a 4°C refrigerator. Following completion of the sucrose protectant phase, the biopsy sample will be embedded in a 15 mm × 15 mm standard cryo-mold filled with optimum cutting temperature compound (OCT) and frozen. These blocks will be stored in a -80°C freezer until cutting. The tissue will be cut and stained according to the methods and using the materials outlined in [Beiswenger et al, 2008](#).

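### The only IENFD test the protocol fixes is change from baseline within each arm; with no stated comparison with placebo, a change unrelated to the drug could be read as an effect or hide one

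*Protocol*

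**What the plan says.** Protocol 13.1.7 sets the IENFD analysis. Each subject's change from the baseline to the terminal biopsy is calculated, "within-group change will be tested using a 2-tailed paired t test", and a P value below .05 is described as "being considered significant". The same paragraph defers Norfolk-QOL-DN, both Toronto scores and the two sensory thresholds: the sentence ends "quantitative vibrations perception will be outlined in the statistical analysis plan". IENFD is not in that deferred list.

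The test serves the first secondary objective in 4.2: "To evaluate the efficacy of WST-057 to increase intraepidermal nerve fiber density (IENFD) present in punch biopsies", measured "at weeks 0 and 24 within the same subject". That objective does not mention placebo.

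The one statement that WST-057 will be compared with placebo stands in 13.1.4, under safety data. Section 13.1.3 compares demographic and baseline data only.

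On the baseline measurement, 7.1.1 says "The baseline punch biopsy will be collected at least 28 days prior to study day 1". The day 1 list in 5.1 includes "Review of IENFD results from the screening calf biopsy" as an eligibility check, and inclusion criterion 8 sets the window at 1 to 10 IENF/mm. The biopsy that admits the subject is therefore also the baseline of the test.

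**The concern.** A paired t test within an arm asks whether mean change differs from zero. It does not ask whether WST-057 did anything that placebo did not. Several influences can move the mean change in every arm alike: the two biopsies are processed months apart, the terminal one should come from a site 2 to 3.5 cm away, the disease has its own course, and selection and baseline share one noisy measurement. Randomisation protects only the contrast between arms, and 13.1.7 does not state that contrast for IENFD.

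Two errors are possible. A common upward shift could be read as nerve regrowth. Conversely, a drug that only slows loss, which 3.1 names as one aim, could show no change or a decline and look ineffective. Running the same test in the placebo arms does not repair this, because the unequal allocation gives the active arms far more power against zero than the placebo arms.

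**Working it through.** **Inputs from the protocol.** About 60 randomised 1:1:4:4 (5.1, 6.1), with 50 completers assumed. The allocation reproduces: 60 × (1, 1, 4, 4)/10 = 6, 6, 24, 24, so pooled placebo is 12. Proportional loss (assumed here) gives 5, 5, 20, 20. The test is two-sided at 0.05 (13.1.7). Section 13 gives no power, effect size or SD, so there is no power figure to reproduce.

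**Assumed input.** A common shift d, in SDs of the change score, in every arm with no drug effect. The protocol gives no value, so a range is shown.

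**Step 1: rejection probability within an arm.** Under a shift d the paired t statistic is noncentral t with n − 1 degrees of freedom and noncentrality d√n. For n = 24 and d = 0.5, noncentrality is 0.5 × √24 = 2.45 and the probability of P < .05 is 0.65. For n = 12 it is 0.5 × √12 = 1.73, giving 0.35. For n = 6 it is 0.5 × √6 = 1.22, giving 0.17.

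**Step 2: at least one dose significant, pooled placebo not.** With independent arms this is [1 − (1 − p24)²] × (1 − p12). At d = 0.5: (1 − 0.35²) × (1 − 0.353) = 0.878 × 0.647 = 0.57.

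| Shift d | One arm, n = 24 | One arm, n = 20 | Pooled placebo, n = 12 | One placebo arm, n = 6 | At least one dose significant (n = 24) | ...and pooled placebo not |
|---|---|---|---|---|---|---|
| 0 | 0.05 | 0.05 | 0.05 | 0.05 | 0.10 | 0.09 |
| 0.2 | 0.16 | 0.14 | 0.10 | 0.07 | 0.29 | 0.26 |
| 0.3 | 0.29 | 0.25 | 0.16 | 0.09 | 0.50 | 0.42 |
| 0.5 | 0.65 | 0.57 | 0.35 | 0.17 | 0.88 | 0.57 |

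If the two placebo arms are tested separately and both must be non-significant, the last figure at d = 0.5 becomes 0.878 × (1 − 0.171)² = 0.60. These are two-sided probabilities; at d = 0 half of the rejections point to worsening.

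**Step 3: the between-arm test in the same setting.** Simulating 24 against 12 subjects, both shifted by 0.5 SD with no drug effect, a two-sample t test rejects with probability 0.050. The common shift cancels.

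**Step 4: regression to the mean from the 1 to 10 window.** Simulation with an assumed between-subject SD of 3 and measurement SD of 1.5 to 2.5 IENF/mm, no drift and no drug effect:

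| Mean of screened population | Mean change (IENF/mm) | Significant increase, n = 24 |
|---|---|---|
| 3 | −0.25 to −0.49 | below 0.01 |
| 5.5 | 0.01 to 0.07 | about 0.03 |
| 8 | 0.28 to 0.68 | 0.09 to 0.16 |
| 10 | 0.52 to 1.22 | 0.22 to 0.42 |

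The sign depends on where the screened population sits relative to the window, which the protocol does not give.

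**Step 5: what a placebo comparison can detect.** Noncentrality is δ√[n1n2/(n1 + n2)], with δ in SDs of change. For 80% power:

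- 48 vs 12: √9.6 = 3.10, δ = 0.92 SD
- 24 vs 12: √8 = 2.83, δ = 1.02 SD
- 40 vs 10: √8 = 2.83, δ = 1.01 SD
- 20 vs 10: √6.67 = 2.58, δ = 1.12 SD

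Power for 24 vs 12 is 28% at a true 0.5 SD and 59% at 0.8 SD.

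**The case against.** The primary objective is safety and tolerability, efficacy is called exploratory in 5.1, IENFD is secondary and no power calculation was attempted. An imperfect test here decides no primary claim. That stands, and it limits the severity.

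A reader might infer that a drug effect would be declared from the paired test. Section 13.1.7 says only that a result is significant and sets no success criterion. The link to drug efficacy comes through objective 4.2, so the supportable wording is that the result could be read that way. A reader might also infer that no placebo comparison of IENFD will be made. The statistical analysis plan is not at hand and nothing in 13.1.7 forbids adding one. What can be said is that the protocol states none and, unlike its treatment of the other efficacy endpoints, does not defer IENFD.

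The drift sizes are assumptions: with none, each arm's error rate is the nominal 5%, and only an upward shift mimics benefit. Regression to the mean is close to nil at a screened mean of 5.5 and can run against the drug, so it should not be presented as a bias in the drug's favour. Nor do the documents support a long fixed gap between slide readings. They fix when the baseline biopsy is collected, but its result need be available only by day 1, about 24 weeks before week 24, and early terminators are biopsied sooner.

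Some safeguards exist. Counting is by a blinded observer, which makes a placebo response in nerve counts implausible, and the untreated thigh is biopsied at both times, which could help expose assay drift. But blinded counting does not remove drift, site difference or natural course, and 13.1.7 specifies no calf-versus-thigh test.

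**Conclusion.** The point holds as a should-fix: the stated rule is wrong as written for an efficacy objective in a placebo-controlled trial. Its size depends on a common shift that the protocol does not quantify. Over the assumed 0 to 0.5 SD, the chance of significance in one 24-subject arm with no drug effect runs from 0.05 to 0.65. The pattern most easily taken as efficacy (a dose significant, pooled placebo not) runs from 0.09 to 0.57, partly because the arms differ in size (24 against 6 or 12). These figures assume normal changes, equal SDs and independent arms. The conclusion does not depend on any particular shift, because the within-arm test cannot separate drug effect from common change at any value. It does not extend to a claim that the trial will report a false effect or that the full analysis plan lacks a between-group test.

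**What to change.** Replace the IENFD rule in 13.1.7 with wording to this effect: the efficacy comparison is the between-group difference in week-24 calf IENFD, adjusted for baseline calf IENFD by ANCOVA, for the combined WST-057 groups versus pooled placebo and for each dose versus pooled placebo, with 95% confidence intervals; within-group paired changes are descriptive. In 4.2, add that the IENFD objective is assessed in comparison with placebo. Any between-group analysis in the statistical analysis plan should be aligned with this text. Another baseline-adjusted between-group method would also serve; the essential point is the contrast with placebo.

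The cost is wording only, with no new visits, biopsies or laboratory work, and it should be done before unblinding. The price is a less favourable-looking result. About 0.92 SD (48 vs 12) or 1.02 SD (24 vs 12) is detectable with 80% power, or 1.01 and 1.12 SD with the planned 50 completers under proportional loss, before a modest gain from the covariate. The paired test reaches 80% power at about 0.60 SD with 24 subjects, but for a question that does not isolate the drug. With 10 to 12 placebo subjects the comparison is mainly an estimate, and the confidence interval should carry the interpretation.

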## **14 STUDY MANAGEMENT AND DATA COLLECTION**

### **14.1 Ethical Conduct of the Trial**

This study will be conducted according to the protocol; 21 CFR parts 50, 54, 56, and 312; the Declaration of Helsinki; and ICH GCP. The Investigator will conduct the trial according to applicable local laws and federal regulatory requirements.

### **14.2 Institutional Review Board**

IRBs must be constituted according to the applicable state and federal requirements (including ICH GCP) of each participating location.

It is the responsibility of the clinical site to submit the protocol, IB, subject ICF, subject recruitment materials (if applicable), and other documentation (as required by the IRB) to its IRB for review and approval. A copy of the written approval must be provided to WinSanTor or designee. The documentation should clearly mention the approval/favorable opinion of the protocol, the subject ICF, and subject recruitment materials (if applicable), including respective version dates. The IRB written approval and a list of the voting members, their titles or occupations, and their institutional affiliations (or the name of the IRB chairperson and Federal Wide Assurance number) must be obtained from the IRB and provided to WinSanTor or designee prior to the release of clinical study supplies to the investigational site and commencement of the study. If any member of the IRB has direct participation in this trial, written notification regarding his or her abstinence from voting must also be obtained.

The clinical site must adhere to all requirements stipulated by its IRB. This includes notification to the IRB regarding: protocol amendments, updates to the subject ICF, recruitment materials intended for viewing by subjects, investigational new drug safety reports, serious and unexpected AEs, reports and updates regarding the ongoing review of the trial at intervals specified by the IRB, and submission of final study reports and summaries to the IRB.

### **14.3 Subject Informed Consent**

Prior to any study-specific procedures being performed, subjects and persons conducting the consent discussion will be required to sign and date the IRB-approved ICF, and each subject will be given a copy. In addition, this information should be recorded in the subject's medical record (source document).

The written consent document will embody the elements of informed consent as described in the Declaration of Helsinki, 21 CFR part 50.25, ICH GCP, and in accordance with any local regulations. The Investigator is responsible for the preparation, content, and IRB approval of the informed consent. The ICF must be approved by the clinical site's IRB and be acceptable to WinSanTor or designee.

The ICF must be written in a language fully comprehensible to the prospective subject. The Investigator or designee shall give the subject adequate opportunity to read the ICF before it is signed and dated. Information will be given in both oral and written form, whenever possible,

and in the manner deemed appropriate by the IRB. Subjects must be given ample opportunity to inquire about details of the study.

#### **14.4 Amendments to the Protocol**

An amendment must be agreed to in writing by WinSanTor or designee and submitted to the Agency as an IND amendment. It must also be submitted to and approved by the IRB for the clinical site before the amendment can be implemented. Written approval of a protocol amendment is not required prior to implementation of changes to the protocol that eliminate immediate hazard to the subject; however, approval must be obtained as soon as possible thereafter. Any agreed amendments must also be signed by the Investigator.

#### **14.5 Study Initiation**

The Investigator must not enroll any subjects prior to the completion of a formal initiation meeting conducted by a representative of WinSanTor or designee. This meeting will include an inventory of study supplies and a detailed review of the study protocol and associated CRFs. The Investigator will not be supplied with study drug until all of the required regulatory documentation has been provided to WinSanTor or designee.

#### **14.6 Study Monitoring**

It is the responsibility of the Investigator to ensure that the study is conducted in accordance with the protocol, ICH GCP, CFR, and other applicable regulatory requirements, and the current Declaration of Helsinki, and that valid data are entered into the CRFs.

To achieve this objective, the study monitor's duties are to aid the Investigator and, at the same time, the sponsor, in the maintenance of complete, legible, well-organized, and easily retrievable data. The study monitor will review the protocol with the Investigator. In addition, the study monitor will explain the Investigator's reporting responsibilities and all applicable regulations concerning the clinical evaluation of the study drug.

The Investigator will permit the representatives of WinSanTor or designee to monitor the study as frequently as WinSanTor (or designee) deems necessary to determine that data recording and protocol adherence are satisfactory. It is estimated that for this study, a site monitoring visit will be conducted for study initiation, after each cohort is completed, and at study termination. The CRFs and related source documents will be reviewed in detail by the study monitor at each visit, in accordance with relevant SOPs and ICH GCP regulations. This includes results of tests performed as a requirement for participation in this study and any other medical records required to confirm information contained in the CRFs, such as past medical history and secondary diagnoses. The Investigator and his/her staff will be expected to cooperate with the study monitor and provide any missing or incomplete information whenever possible.

All monitoring activities will be reported and archived. In addition, monitoring visits will be documented at the investigational site by signature and date on the study-specific monitoring log.

## 14.7 Case Report Form

The eCRFs will be provided by validated electronic data capture screens. All subject data generated during the study will be recorded on the source documents and transcribed to the electronic data capture screens through a Web browser for entry into a validated electronic database by way of a secure internet connection.

The Investigator and clinical research associate (CRA) will ensure that all data are entered promptly, completely, and accurately and conform to source documents, in accordance with specific instructions accompanying the eCRFs. Any corrections will be recorded by an audit trail. The audit trail will include the user ID of the person making the change and the date the change was made and an explanation why the change was made.

The study monitor will verify the entered data against the source document and issue manual queries. The query text will be manually entered by the monitor. These queries will then be available for the site entry personnel to respond.

WinSanTor will only consider eCRFs to be complete when each eCRF has been reviewed and approved by the Investigator, indicating their assurance of the accuracy of all recorded data. It is expected that the Investigator and his/her staff will cooperate with the monitoring team and provide any missing data in a timely manner.

Laboratory data will be collected electronically and transferred to the CRO handling the eCRF data for integration with the eCRF data.

The 12-lead ECGs will be digitally recorded after a 10-minute rest in the supine position. All ECGs will be over-read by an appropriately qualified physician and the data entered in the subject's eCRF or via validated direct electronic transfer for integration with the eCRF data.

For both of these datasets, a data format will be agreed upon between the CRO handling the clinical study data and the laboratory and ECG vendors. The data management programming group at the CRO will reconcile the external data with eCRF data. Discrepancies will be first addressed with the lab or ECG vendors. If data changes are required to the database, then queries will be issued. If external data need to be modified, the laboratory or ECG vendor will provide updated data.

## 14.8 Verification Procedures

In fulfillment of their obligations to WinSanTor and to verify compliance with this protocol, ICH GCP, and the CFR, the Investigator is required to authorize direct access to the subject's medical records by WinSanTor or designee, IRBs, and regulatory authorities.

It is the Investigator's obligation to ensure documentation of all relevant data in the subject's source document record. The subject's original data may not be recorded directly into the eCRF, but documented in source: medical history/concomitant disease, subject ID, confirmation of informed consent and the date of study enrollment, visit dates, administration of study medications, AEs (start and stop dates), and all concomitant medications (start and stop dates).

The Investigator will maintain a subject identification code list to enable unambiguous identification of each subject's name and corresponding subject number. The subject identification code list is an essential document and will be maintained according to ICH GCP guidelines.

## **14.9 Retention of Records**

All documentation pertaining to the study will be kept by WinSanTor or designee in accordance with Agency regulations.

The study site will maintain a study file, which should contain the IB; protocol; drug accountability records; study correspondence; and other study-related documents to establish that the clinical trial is conducted in accordance with GCPs and the Regulations.

The sponsor shall maintain complete and accurate records in respect of the use of a drug in a clinical trial, including: a copy of all versions of the IB for the drug; records respecting each change made to the IB, including the rationale for each change and documentation that supports each change; records respecting all adverse events in respect of the drug that have occurred inside or outside Canada, including information that specifies the indication for use and the dosage form of the drug at the time of the adverse event; records respecting the enrolment of clinical trial subjects, including information sufficient to enable all clinical trial subjects to be identified and contacted in the event that the sale of the drug may endanger the health of the clinical trial subjects or other persons; records respecting the shipment, receipt, disposition, return and destruction of the drug; for each clinical trial site, an undertaking from the qualified investigator that is signed and dated by the qualified investigator prior to the commencement of his or her responsibilities in respect of the clinical trial, that states that: the qualified investigator will conduct the clinical trial in accordance with GCPs, and the qualified investigator will immediately, on discontinuance of the clinical trial by the sponsor, in its entirety or at a clinical trial site, inform both the clinical trial subjects and the REB of the discontinuance, provide them with the reasons for the discontinuance and advise them in writing of any potential risks to the health of clinical trial subjects or other persons; for each clinical trial site, a copy of the protocol, ICF and any amendment to the protocol or ICF that have been approved by the REB for that clinical trial site; and for each clinical trial site, an attestation, signed and dated by the REB for that clinical trial site, stating that it has reviewed and approved the protocol and ICF and that the board carries out its functions in a manner consistent with GCPs. The sponsor shall maintain all records referred to in the applicable Regulations for a period of 25 years.

The Investigator agrees to keep records and those documents that include (but are not limited to) the identification of all participating subjects, medical records, study-specific source documents, source worksheets, all original signed and dated ICFs, copies of all CRFs, query responses, and detailed records of drug disposition, to enable evaluations or audits from regulatory authorities and WinSanTor or its designee(s).

The Investigator shall retain records required to be maintained under this part for a period of 25 years. However, these documents should be retained for a longer period if required by the

applicable regulatory requirement(s) or if needed by the sponsor. In addition, the Investigator must make provision for the subject's medical records to be kept for the same period of time.

No data should be destroyed without the agreement of the sponsor. WinSanTor will inform the Investigator in writing when the trial-related records are no longer needed.

Subjects' original data will be archived in accordance with the archiving regulations or facilities of the investigational site.

